#### Data collections

For the baseline study, data collection among students at the beginning of year 7 (age 13) and school coordinators are collected in the autumn 2017. Follow-ups are collected three times: at the end of year 7, 8 and 9 (age 15). Students are followed by using information on their name, birthday, class and school. This information is used for following students over time only. All further work with the data is in a non-identifiable version. Students changing to a school outside the evaluation are omitted from the study. Information about signed smoke free agreements is collected through the student questionnaires in each follow-up. To gain information about the curricular activities, school coordinators are asked to answer few monthly questions by email. Enforcement of the smoke free school time is measured by questions to students and to school coordinators in all questionnaires.

Students answer internet based questionnaires in the classroom after a standardized instruction given by the teacher. The students are informed that participation is voluntary and that their responses will be treated with confidentiality.

### Process evaluation

As was the case for the evaluation of X:IT [19–21, 25], we will conduct a detailed process evaluation among teachers and students focusing especially on those from low SEP. The process evaluation is based on questions added to the student and school coordinator questionnaires concerning the implementation of the study, e.g. the fidelity and dose of the intervention. Further, we will conduct ethnographic fieldwork at schools and qualitative interviews with students, school coordinators and other teachers involved in X:IT II. Information about the actual curricular activities is collected through monthly electronic questionnaires to teachers.

As the quality of implementation has a great impact on the conceivable effects, the process evaluation will have a specific focus on implementation. The organizational capacity for implementation at each school will be assessed through the baseline questionnaires for school coordinators. These measures are based on theories by Domitrovich et al. (2008) [34] and Saccia et al. (2015) [35], hence we will measure Motivation (i.e. the perceived relative advantage of X:IT compared to other programs, the complexity of X:IT and the priority for the school), General organizational capabilities (i.e. school culture, climate and leadership), and Innovation-specific capabilities (i.e. knowledge, skills and abilities needed for the intervention and the presence of a program champion). Further, the actual obtained implementation will be assessed at all follow-ups by both school coordinators and students, based on implementation measures developed in the evaluation of X:IT [20].

The qualitative data will focus on the school coordinator and teacher’s implementation of the X:IT II intervention. Thus, we will explore: 1) the teacher’s appraisal and reaction to the intervention and activities, 2) how the teachers experience and understand the problem that the intervention seeks to address, and 3) how the intervention activities are implemented in practice [36–38]. To understand adolescent’s smoking related behavior, we will investigate the influence of adolescent’s social relations and smoking in the daily environment [39, 40]. This will help us understand how the students perceive and receive the intervention.

The ethnographic field study (comprising observations and interviews) will provide in-depth knowledge about contextual circumstances regarding the implementation, delivery and reception of the intervention. These methods, will enable us to account for the context in which events occur and uncover social patterns, for example, which relationships are important for actions related to the X:IT intervention and hence smoking [41]. By being physically present at schools, taking part in and observing the students and teachers carrying out their daily activities, we will be able to understand how the intervention is practiced at schools and how it and smoking is perceived by students and teachers [41].

### Statistical methods

#### Data process and analyses

The analyses of effect will be based on the principles of the difference-in-difference approach. The difference-in-difference design compares outcomes after and before an intervention between an exposure group and a comparison group [32]. In the evaluation of X:IT II, we will consider the group of students with high SEP as the comparison group (group C) and students with low SEP as the exposed group (group E). This means that the change in outcomes can be estimated as (Cafter-Cbefore) - (Eafter-Ebefore). If X:IT II works equally well for students from both high and low SEP, the difference-in-difference estimate is equal to 0 which is the aim of X:IT II.

The difference-in-difference estimates will be conducted in regression models rather than by simple subtraction which allows adjusting for confounders. We will conduct both per-protocol analyses and intention-to-treat (ITT) analyses using multiple imputation of missing values. Furthermore, we will use statistical methods that take into account the multilevel structure of the design of the study.

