## Background

In Denmark, as well as in most Westernized countries, smoking is more prevalent among adolescents from lower socioeconomic positions (SEP) [1]. While 8 % of 15-year old Danish adolescents from higher SEP smoke (daily or less), up to 24% of adolescents whose parents receive welfare benefits are smokers [2]. Furthermore, adolescents from low SEP seem less likely to quit smoking in adulthood [3]. Public health interventions to reduce risk behaviours (e.g. smoking) should aim at being equally effective across socioeconomic groups or at being more effective among individuals from low SEP [4].

Interventions addressing health and health behaviours in childhood or adolescence have the potential to prevent or decrease socioeconomic inequalities in health behaviours later in life [5]. On the other hand, interventions themselves may generate or increase socioeconomic inequalities in health behaviours, e.g. in smoking [6]. This is problematic to the extent that interventions may be less effective or have counter-effects in the most at risk groups, often low SEP. Socially differential effects of interventions may arise at a number of points in the implementation process of an intervention, including intervention efficacy, service provision or access to materials and tools, uptake, and compliance [7]. Most intervention studies on smoking have not addressed these aspects and therefore, the mechanisms behind any inequality or lack of inequality of the effect of interventions are unknown. It has been argued that interventions targeting individual aspects related to behavioral change are more likely to widen social inequalities compared to interventions targeting the environment, because the interventions targeting the individual directly require more effort and resources from each individual [8].

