### Evaluation

#### Design

The X:IT II intervention will be evaluated by means of effect in a difference-in-difference design. Hence, all participating schools will receive the same intervention, and students from high and low social classes will be compared in the difference-in-difference design [32]. Process evaluation will be conducted at specific time points during the intervention period. Data collections are shown in Table 2.

**Table 2 Tab2:** Data collection of the X:IT II study – timeline, instrument and source of data

	Baseline September 2018	Intervention	Follow-up 1 May 2018	Intervention	Follow-up 2 April 2019	Intervention	Follow-up 3 April 2020
Students	Questionnaires (students start year 7)		Questionnaires (students end year 7)	Observations and interviews	Questionnaires (students end year 8)		Questionnaires (students end year 9)
School coordinators	Questionnaires		Questionnaires		Questionnaires		Questionnaires
Teachers		Monthly questionnaires on curricular activities (September – June)		Observations and interviews Monthly questionnaires on curricular activities (September – June)		Monthly questionnaires on curricular activities (September – June)	

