One of the limitations of this study is that we did not succeed in recruiting the required number of schools for a randomized design. The clustering of smoking in schools and classes leads to the need of a very high number of schools for an RCT, in this case 78 schools for intervention and 78 for comparison. The main purpose of the X:IT II study is to examine the differences between high and low SEP and the mechanisms behind these differences. The difference-in-difference design suits this purpose. There are two main assumptions to the difference-in-difference design, the assumption of parallel trends and the assumption of common shocks. First, the parallel trends assumption states that trends in outcomes between the exposed and comparison groups are parallel prior to the intervention. As we know from the literature, that smoking is more prevalent among both adolescents and adults from lower SEP [1, 43], it is not possible to fulfill this assumption. On the other hand, at the beginning of grade 7, very few students have become smokers and as such a trend in smoking is not calculable in this age group. We expect that the second assumption of common shocks stating that any events occurring during or after the intervention will equally affect the exposure and comparison groups, will be fulfilled. Power calculations for the difference-in-difference design showed a need for 48 schools, which was fulfilled in the recruitment where 57 schools gave consent to participate. However, as previously described only 46 schools participated in the baseline data collection.

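### A difference-in-difference of 0 does not mean equal benefit in high and low SEP when both groups are treated and smoking diverges by SEP from a near-zero start

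*Protocol article*

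**What the plan says.** Under Data process and analyses, high-SEP students are the comparison group (C), low-SEP students are the exposed group (E), and "the change in outcomes can be estimated as (Cafter-Cbefore) - (Eafter-Ebefore"). The interpretation follows directly: "If X:IT II works equally well for students from both high and low SEP, the difference-in-difference estimate is equal to 0". The article calls this value the aim of X:IT II. The next paragraph adds that "The difference-in-difference estimates will be conducted in regression models rather than by simple subtraction which allows adjusting for confounders". No link function, scale or test is named.

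The Design section states that "all participating schools will receive the same intervention, and students from high and low social classes will be compared". There is no untreated group.

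The Discussion says of parallel trends that "it is not possible to fulfill this assumption", and adds that "at the beginning of grade 7, very few students have become smokers". It still judges the design suited to the study's main purpose, the comparison of high and low SEP.

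The Background gives the social gradient at the end of the age range: "8 % of 15-year old Danish adolescents from higher SEP smoke (daily or less"), against "up to 24% of adolescents whose parents receive welfare benefits are smokers".

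**The concern.** A difference-in-difference isolates an effect when one group is untreated and the two groups would otherwise have changed in parallel. Neither condition is met here. With both groups treated, the formula adds two quantities that the data cannot separate: how far smoking in the two SEP groups would have drifted apart between grades 7 and 9 anyway, and any difference in how well the programme works. The estimate is 0 under equal benefit only if the first quantity is 0. The article's own facts, few smokers at the start and an unequal prevalence at 15, imply that it is not.

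This comparison is the main purpose of the study. If the sentence guides interpretation, a programme that helps low-SEP students just as much, or somewhat more, could be reported as failing them. The third hypothesis asks only that the reduction in low SEP be the same or greater.

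**Working it through.** **Inputs from the article.** Age-15 smoking is 8% in higher SEP and up to 24% where parents receive welfare benefits (Background). The 25% relative reduction is from Hypotheses and Power calculations. School size 50 and intra-class coefficient 0.053 are from Power calculations. There are 46 schools (Recruitment plan).

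**Assumptions.** The 8% and 24% are untreated levels. Baseline smoking is 0% in both groups, and is varied below because the article gives no figure. The milder gaps, the low-SEP shares, a two-sided 5% test and 46 × 50 = 2300 students are also assumed.

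**1. The article's formula under equal benefit.** DiD = (C after − C before) − (E after − E before). The stated value is 0.

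| Scenario (baseline 0/0) | C after | E after | DiD, points |
|---|---|---|---|
| No effect in either group | 8% | 24% | -16 |
| Equal 25% relative reduction | 6% | 18% | -12 |
| Equal absolute reduction (e.g. 4.5 points) | 3.5% | 19.5% | -16 |
| Equal 25% reduction, gap 8% vs 16% | 6% | 12% | -6 |
| Equal 25% reduction, gap 8% vs 12% | 6% | 9% | -3 |

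The stated 0 is not reproduced in any row, whether equal benefit is taken as relative or absolute.

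**2. The reverse direction.** Suppose high SEP falls by 25%, from 8% to 6%. DiD = 0 then needs low SEP to fall from 24% to 6%, and 1 − 6/24 = 75%. A value of 0 would here signal a much larger benefit in low SEP. On the percentage-point scale, 0 is therefore neither necessary nor sufficient for equal benefit.

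**3. Other baselines** (8% vs 24%, uptake reduced by 25% in both groups). With 1%/1%, the after values are 1 + 7 × 0.75 = 6.25% and 1 + 23 × 0.75 = 18.25%, so DiD = 5.25 − 17.25 = -12.0. With 1%/3%, 5.25 − 15.75 = -10.5. With 2%/6%, 4.5 − 13.5 = -9.0.

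**4. Ratio scales, same scenarios.**

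| Baseline C/E | Log-risk DiD | Log-odds DiD |
|---|---|---|
| 1%/1% | ln(6.25/1) − ln(18.25/1) = -1.07 | -1.21 |
| 1%/3% | ln(6.25/1) − ln(18.75/3) = 0 | -0.12 |
| 2%/6% | ln(6.5/2) − ln(19.5/6) = 0 | -0.11 |

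The bias is nil or small only where the baseline SEP ratio already equals the later 1:3. With almost no smokers at baseline, that ratio is poorly estimated.

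**5. How often a test would reject 0 under equal 25% reductions.** With zero baselines, SE = √[pC(1 − pC)/nC + pE(1 − pE)/nE], multiplied by √3.597 when the full design effect 1 + 49 × 0.053 = 3.597 is applied.

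| Gap | Low-SEP share 10% / 20% / 40%, no clustering | Same shares, full design effect |
|---|---|---|
| 8% vs 24% | all over 99% | 69% / 92% / 99% |
| 8% vs 16% | 78% / 96% / 99.8% | 30% / 50% / 72% |
| 8% vs 12% | 33% / 55% / 75% | 13% / 19% / 28% |

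For a contrast made largely within schools the full design effect may be too severe, so the truth may lie between the two columns.

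**The case against.** The strongest reply has four parts.

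- **Disclosure.** The Discussion admits that parallel trends fail and lists the lack of randomisation as a limitation. That stands in part. But the caveat is never carried back to the sentence that gives 0 its meaning. The remark that no trend can be calculated before grade 7 does not help, because the problem is divergence after baseline.

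- **Scale and adjustment.** The estimates are to come from regression models, possibly on a ratio scale, adjusted for confounders. Parental and friends' smoking are measured at baseline and might absorb some of the natural divergence. It therefore cannot be asserted that the final model works in percentage points. But a ratio scale removes the problem only in the special case shown above, and nothing in the article shows that adjustment would remove divergence by SEP itself.

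- **Inputs.** The 24% is an upper figure for one subgroup, not for the whole low-SEP group, and Table 3 codes economically inactive families as a separate category. With a low-SEP share of 10% to 40%, 8% and 24% imply 9.6% to 14.4% overall, below the 17.9% in the power calculation, which would need a share of (17.9 − 8)/16 = 62%. The levels are illustrations, and -12 lies towards the large end.

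- **No formal rule.** The sentence states an aim, with no test or margin. A reader might infer that the trial is bound to declare X:IT II inferior in low SEP, or that 0 would be rejected almost always. The document does not support either: it specifies no rejection criterion, and the probability falls to about 13% under the mildest gap with full clustering.

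**Conclusion.** The statement that equal benefit gives a difference-in-difference of 0 is wrong as written and conflicts with what the article concedes about parallel trends and near-zero baseline smoking. Under an identical 25% reduction, with zero baselines, the formula gives about -3 to -12 percentage points for age-15 gaps from 8% vs 12% to 8% vs 24%. It gives -16 with no effect at the widest gap. The direction is the same throughout: equal benefit looks like less benefit in low SEP.

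The size rests on the assumed baselines and on reading the Background figures as untreated levels. The fault itself needs only two things: no untreated group, and natural divergence on the scale analysed. How often a test would mislead is not settled by the article.

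**What to change.** Delete the sentence that equates a zero estimate with equal effect. State the scale of the regression. Report the within-X:IT II estimate as the change in the social gap in smoking during grades 7 to 9, without a claim about differential effectiveness. This costs only rewording and needs no new data. The price is a more modest main conclusion.

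As an optional sensitivity analysis, SEP-specific changes could be set against those in the 41 control schools of the first X:IT trial, reporting the ratio of relative reductions, where 1 means equal effect. This requires that those data are available with comparable SEP coding, which the article does not establish. Its limits should be stated with it:

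- Secular change between the two periods may differ by SEP.
- The August 2012 ban on smoking on school grounds fell within the first trial.
- The X:IT II schools are self-selected: 60 of the 300 contacted showed interest and 46 supplied baseline data.
- Precision will be lower.

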### Hypotheses

Based on these modifications of the X:IT intervention, we hypothesize that:the X:IT intervention material, carefully developed to take into account the intellectual skills and academic performance of adolescents´ and their parents´, will improve the reach of the intervention among low socioeconomic background.the X:IT intervention study will have an overall effect of a 25% reduction in smoking uptake at age 13.the X:IT intervention study will reduce smoking uptake among low socioeconomic position adolescents to the same extent or more than among adolescents with a high socioeconomic position background.

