## Discussion

The primary focus of this study is to evaluate the smoking preventive intervention – X:IT II. We expect the revised version of the X:IT intervention to be equally successful in preventing smoking uptake in adolescents from high and low socioeconomic backgrounds. Smoking prevalence is higher among low SEP adolescents [1] and contributes to a large extent to the social inequality in health over the lifetime [5].

Public health interventions are often accused of leading to higher social inequality when implemented across populations [4]. School-based interventions to prevent smoking can also widen this inequality, however studies have also been found to reduce the gap; secondary analyses of three overall effective school-based European smoking interventions showed mixed results. One seemed to widen socioeconomic inequality, while the two other studies showed mixed results depending on which measure of socioeconomic status that were used [42]. One of the conclusions from the study was that adolescent smoking is also influenced by factors outside the school, especially smoking by parents and other significant relations, which are important to include when aiming at reducing the social inequality in intervention effects [42]. The changes conducted in the X:IT II intervention are based on thorough interview work with the target population of children from low social class and their parents. The changes should therefore be highly relevant and target some of the specific problems related to a smoking preventive intervention, such as the X:IT intervention.

The X:IT II intervention is based on an intervention which has been thoroughly evaluated and has proven effective, especially when implemented correctly. The X:IT II intervention target adolescent smoking from multiple levels simultaneously; the individual level, the family level, and the school level. This is recommended by the literature and must be considered state of the art in school-based smoking interventions [11]. The X:IT intervention is developed and adjusted by the Danish Cancer Society and will be evaluated by the Centre for Intervention Research. Especially in an intervention which is not a randomized controlled trial it is of great value, that the evaluating organization is independent from the organization that developed and implemented the intervention.

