To further improve the evidence from this study, a thorough process evaluation is planned including both qualitative and quantitative methods. The qualitative evaluation will seek to understand how teachers work with the intervention and under which circumstances the best implementation is obtained. Further, we will obtain knowledge and understanding on how students perceive and receive the intervention. The quantitative process evaluation will, as was the case in the former evaluation of X:IT, be based on students receiving the intervention. Also, school capacity to implement, as well as the actual obtained implementation, will be assessed. Like in the X:IT study [20, 25], we will conduct analyses taking the actual implementation into account in the effect evaluation. Hereby, we will be able to draw conclusions about the effectiveness of the X:IT evaluation. We will examine intervention effects in relation to the actual implementation at the school as well as the individual level. Numbers of students receiving the intervention in X:IT II is almost equal to the group of intervention pupils from the first evaluation. Analyses will therefore be comparable to each other.

If shown to be effective, the X:IT II study will provide important information on how to prevent smoking uptake effectively also among the group of adolescents from low socioeconomic backgrounds who are currently at higher risk of smoking uptake in Denmark.

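### The aim is set as a difference-in-difference of 0 between high and low SEP, but that contrast measures only differential change and cannot show that X:IT II prevents smoking

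*Protocol article*

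**What the plan says.** The Design section under Evaluation states that "all participating schools will receive the same intervention, and students from high and low social classes will be compared". There is no untreated group.

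The section Data process and analyses bases the effect analyses on this comparison. High SEP is the comparison group (C), low SEP is the exposed group (E), and the estimate is (C after − C before) − (E after − E before), to be fitted in regression models. It adds that, if the programme works equally well in both groups, "the difference-in-difference estimate is equal to 0 which is the aim of X:IT II".

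Other sections look for more than a difference between groups:
- One item under Hypotheses is that the study "will have an overall effect of a 25% reduction in smoking uptake at age 13". Another is that uptake in low SEP will fall "to the same extent or more than among adolescents with a high socioeconomic position background".
- The Discussion expects the programme to be "equally successful in preventing smoking uptake in adolescents from high and low socioeconomic backgrounds", and closes with "If shown to be effective, the X:IT II study will provide important information on how to prevent smoking uptake effectively".

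The Discussion also names the SEP difference as the main purpose, and concedes that the parallel-trends assumption cannot be fulfilled.

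**The concern.** The text goes from equal benefit to an estimate of 0 and then makes 0 the goal. The reverse inference fails. Because both groups are treated, the contrast estimates a difference between two effects, not an effect. A result of 0 is compatible with equal prevention and with none.

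The null case is realistic. The section on the first X:IT trial reports that implementation declined and that no effect could be shown after the second year, and X:IT II runs for three school years. The Background links the evaluation to a possible national scale-up. A statement that the programme works equally well across social groups could therefore carry weight that the statistic cannot support.

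**Working it through.** **Inputs from the article**
- Every school is treated (Design).
- The estimator and its target of 0 (Data process and analyses).
- Grade 9 smoking of 17.9%, expected to fall by 25% to 13.4% (Power calculations). Check: 17.9 × 0.75 = 13.425, which agrees.
- Smoking at age 15 of 8% in higher SEP and up to 24% where parents receive welfare benefits (Background).
- Very few smokers at the start of grade 7 (Discussion). No figure is given, so baselines of 0–2% in high SEP and 0–6% in low SEP are assumed below.

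**Step 1: what the contrast contains.** Let T_C and T_E be the rises in smoking that would occur without the programme, and d_C and d_E the absolute reductions that it causes. Then

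DiD = (T_C − d_C) − (T_E − d_E) = (T_C − T_E) − (d_C − d_E).

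With parallel untreated trends (T_C = T_E) and equal absolute effects (d_C = d_E), DiD = 0 whatever the size of the effect, including none.

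**Step 2: the plan's target of 0 under parallel trends.** For illustration, take the grade 9 figures for both groups and an assumed 1% baseline in each.
- No effect: (17.9 − 1) − (17.9 − 1) = 0.
- Full planned reduction in both: (13.4 − 1) − (13.4 − 1) = 0.

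The target is met in both cases.

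**Step 3: the article's own SEP rates.** A 25% relative reduction takes 8% to 6% and 24% to 18%. From a baseline of 0:
- No effect: (8 − 0) − (24 − 0) = −16 points.
- 25% in both groups: (6 − 0) − (18 − 0) = −12 points.

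Over the assumed baselines:

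| Baseline high / low SEP | No effect | 25% reduction in both |
|---|---|---|
| 0% / 0% | −16 | −12 |
| 1% / 1% | −16 | −12 |
| 1% / 3% | −14 | −10 |
| 2% / 4% | −14 | −10 |
| 2% / 6% | −12 | −8 |

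No entry is 0. From a zero baseline with a 25% fall in high SEP, low SEP would need a fall of 1 − 6/24 = 75% for the estimate to reach 0.

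The 24% is a top figure for one part of low SEP. For a general untreated low-SEP rate p and a zero baseline, the two results are 8 − p and 0.75 × (8 − p). Both shrink towards 0 as p falls towards 8%.

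**Step 4: ratio scale.** The article does not fix the regression scale. With baselines of 1% and 3%, the ratio of risk ratios is (8/1)/(24/3) = 1.00 with no effect and (6/1)/(18/3) = 1.00 with 25% in both. On this scale an equal relative effect cancels, just as an equal absolute effect cancels under subtraction.

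**The case against.** A reader might infer that an ineffective X:IT II will meet the aim in any case and will be reported as a success. The documents do not support that. A null programme gives 0 only if untreated trends are parallel, or on a ratio scale if the SEP ratio stays constant. The Discussion says that parallel trends cannot be fulfilled. With the article's rates and its subtraction formula, a null programme lands at about −16 and would be read as unequal. Nor does every common effect cancel: a 25% relative reduction in both groups moves the estimate from −16 to −12.

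The Discussion sentences are also an expectation and a conditional. Neither says that an estimate of 0 will be taken as proof of effectiveness. The article names the SEP difference as its main purpose, plans analyses by actual degree of implementation from which effectiveness is to be judged, and already lists smoking at grades 7, 8 and 9 as a primary outcome.

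All of this tempers the point but does not remove it. Telling −12 from −16 requires the untreated rates, which means an outside reference that the reading rule does not call for. The implementation analyses are non-randomised and leave the rule unchanged. A main purpose confined to SEP differences is a reason to confine the conclusions in the same way. The matter is also not one of detail left to an analysis plan, because the article itself fixes the estimator, its target and its interpretation.

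**Conclusion.** The point holds in a limited form. The cancellation follows from the design and needs no assumed figure: with both SEP groups treated, the contrast shows differential change only, and 0 is not evidence of prevention. Under parallel untreated trends, an ineffective programme could be reported as working equally well.

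Without parallel trends, 0 is not the right target either. At a zero baseline, the Background rates imply about −16 points for no effect and about −12 for an equal 25% relative reduction. Over the assumed baselines the ranges are −12 to −16 and −8 to −12. These sizes are upper bounds, because 24% does not describe the whole low-SEP group.

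The overall 25% hypothesis has no comparator within this design. That is a neighbouring problem which rewording the rule would not cure.

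**What to change.** In Data process and analyses, delete the clause that makes 0 the aim, and state that an estimate near 0 means no difference in change between SEP groups.

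There and in the Discussion, describe the programme as working equally well, equally successful or effective only if smoking in each SEP group is also shown to be below a stated external reference. If no such reference can be named, limit the conclusions to differential change.

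Report smoking at grades 7, 8 and 9 in each SEP group beside the difference-in-difference estimate.

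The cost is a change of wording and a few more reported estimates from data already being collected. The downside is a narrower claim.
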